### Statistical analysis

#### Determination of sample size

The trial was designed to test whether the Minipally intervention was superior to the usual educational in terms of stress regulation and children’ behaviors. We used Heo’s statistical procedure for cluster randomized trial in our sample size estimation [33]. That is, we based our calculation on the expected mean number of groups within each child care centers –i.e. 2 groups per child care center. Recall that the CCS are our randomization units. Power calculation indicated that 19 child care services would allow to detect a medium size effect of the intervention on the selected outcomes, with 90% power at a 2-sided significance level of α = 5%. Our model can be stated as Y_ijk_ = β_0_ + δX_i_ + u_i_ + u_j(i)_ + e_ijk_; where Y_ijk_ is the post-intervention response of the i^th^ study participant in the j^th^ educator group nested the k^th^ child care services, β_0_ correspond to baseline value of our primary outcome, δX_i_ assess the main effect of the intervention (where X = 0 for waiting list group and X = 1 for the experimental group), and the last three terms are random effects at every level of the trial analysis [33].

Data will be analyzed per the intention-to-treat principle where all participants are considered within their assignment group regardless of the number of Minipally sessions they received. Every child whose parents consented to the evaluation will be included for analysis if they completed at least one assessment (i.e. pre or post-intervention).

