### Testing the impact of the intervention

#### Child behaviors

We expect that children in the Minipally intervention condition will have better social behaviors -higher levels of prosocial behaviors’ and lower levels of opposition, hyperactivity, inattention and physical aggression disruptive behaviors- as compared to children in the waiting list control group in post-intervention. We will use multilevel models where the child’ behaviors in pre-intervention will be considered as a covariate. We will thus 1) account for initial variation in children’s behaviors, and 2) account for the nested structure of the data: children are nested in childcare’s group (i.e. *n* = 8 children per educators) and the childcare’s groups are nested in child care services (i.e. *n* = 1 to 4 groups of preschoolers per child care services).

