### Stress regulation

We hypothesized that children receiving the Minipally program will have better levels of stress regulation (i.e. better diurnal salivary cortisol patterns) at the end of the 8 months intervention than children in the waiting list control group. To model the impact of intervention on preschooler’ stress level, we will use a growth curve model accounting for time variation in cortisol, as cortisol samples were taken three times a day (at the arrival to the CSS, midmorning and 30 min after the afternoon nap). We expect to find a significant difference between the mean slope of cortisol secretion between the intervention and the control group in post-intervention, but not in the intercept levels. Growth curve models also account for the non-independence of repeated measures by modeling multiple data points as nested within individuals, which further allows for missing data. This technic accounts for shared variance within subjects while modeling between-subject differences. The normality assumptions for all our potential covariates and models will be assessed using standard statistical methods and comparison of residual versus predicted plots and residual versus normal scores.

Note that prior to any impact analyses, we will examine the cortisol data for extreme values. Cortisol outliers will be winsorized at >3 standard deviations ud/dL to ensure that extreme values do not exert a disproportionate influence on analysis. Cortisol values have skewed distribution and therefore will be transformed using Log 10. A constant of 1 will be added to original concentration [Log 10 (concentration + 1)] to assure positive transformed cortisol data. We will then use univariate and multivariate models to assess several factors known to potentially affect cortisol secretion (e.g. general sleep, general health, medication) and control for them in later analyses.

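### For the BEH behaviour ratings, the promised analysis set (a pre or a post assessment) cannot be filled by the stated model, which as written needs both scores

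*Protocol article*

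**What the plan says.** The intention-to-treat paragraph under Determination of sample size makes two commitments. Children stay in their assigned arm whatever number of sessions they received, which is sound and not at issue here. The second fixes who is analysed: "Every child whose parents consented to the evaluation will be included for analysis if they completed at least one assessment". The parenthesis that follows makes clear that either the pre or the post assessment is enough.

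The same section writes out a model in which Y "is the post-intervention response of the i^th^ study participant" and the term β0 is said to "correspond to baseline value of our primary outcome". For the behaviour outcomes, the Child behaviors section is explicit: "We will use multilevel models where the child’ behaviors in pre-intervention will be considered as a covariate". The contrast of interest is at the second visit, with intervention children assessed "as compared to children in the waiting list control group in post-intervention".

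The only remark on missing data in the analysis sections is under Stress regulation. It concerns the cortisol growth curve, which works by "modeling multiple data points as nested within individuals, which further allows for missing data".

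**The concern.** A child rated only at T1 has no response in a model of the T2 score. A child rated only at T2 has no value for the T1 covariate. Unless something further is done, neither enters the fit, so the behaviour analysis becomes a complete-case analysis under an intention-to-treat description that says otherwise.

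Such children should be expected. T1 is in October and T2 in June, and the Abstract names turnover of preschoolers among the significant challenges. Parents and educators knew the allocation after randomization and are also the BEH raters. Who is counted in one of the two primary outcomes should therefore follow from the plan, not from how a program treats incomplete rows.

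**Working it through.** **1. Stated rules against each type of child (BEH ratings)**

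| Scores available | In the stated analysis set? | T2 response present? | T1 covariate present? | Used by the model as written? |
|---|---|---|---|---|
| T1 and T2 | yes | yes | yes | yes |
| T1 only | yes | no | yes | no |
| T2 only | yes | yes | no | no |

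The equation under Determination of sample size has no separate slope term for baseline; its text calls β0 the baseline value. Read as a plain intercept, that equation alone would admit a T2-only child. The Child behaviors section removes the doubt, because it makes the pre-intervention score a covariate. The T1-only child has no response on either reading.

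**2. The other primary measures**

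- Cortisol: the growth curve runs over the three samples of the day, and no pre-intervention covariate is named, so a T2-only child can contribute. The expected effect is a "significant difference between the mean slope of cortisol secretion between the intervention and the control group in post-intervention". A T1-only child adds nothing to that contrast unless the T1 samples are modelled too, which the article does not say.
- Research-assistant observation: this is a tally for the whole classroom, so a child-level analysis set does not apply.

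**3. Size of the gap**

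Inputs: 362 children (Abstract and Discussion). No missingness rate is given, so assume that each of the T1 and T2 scores is missing independently with probability p.

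- At least one score: 362 × (1 − p²)
- Both scores: 362 × (1 − p)²
- Share of the promised set left out: 1 − (1 − p)²/(1 − p²) = 2p/(1 + p)

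| p | At least one | Both | Left out | Share of promised set |
|---|---|---|---|---|
| 5% | 361 | 327 | 34 | 10% |
| 10% | 358 | 293 | 65 | 18% |
| 15% | 354 | 262 | 92 | 26% |
| 20% | 348 | 232 | 116 | 33% |

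As a check, one simulated data set of 362 children at p = 15% had 354 with at least one score. The post-on-pre mixed model used 263 of them. The same data laid out with both scores as responses retained all 354.

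**4. Power**

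The article's figure is 90% power, two-sided 5%, with 19 CCS and a medium effect. It gives no numerical effect size or intraclass correlation (ICC), so the figure cannot be reproduced uniquely. Assume d = 0.5, 10 and 9 CCS per arm, n2 = 2 groups per CCS, n1 children per group, and one ICC r within and between groups of the same CCS:

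- Variance of the difference = [1 + n1(n2 − 1)r + (n1 − 1)r]/(n1 n2) × (1/10 + 1/9)
- Power = Φ(d/SE − 1.96)

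With 8 children per group (304 in all), 90% is reached at an ICC of about 0.054. With 362 children (362/38 = 9.53 per group), it is reached at about 0.064. The stated figure is plausible but not confirmable.

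At ICC 0.05 with 362 children, the bracket is 1 + 0.476 + 0.426 = 1.903. The variance is 1.903/19.05 × 0.2111 = 0.0211, SE = 0.145, and power = Φ(3.44 − 1.96) = 93.1%. Losing children evenly across groups gives:

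| Children analysed | Power at ICC 0.05 |
|---|---|
| 362 | 93.1% |
| 326 (10% fewer) | 91.8% |
| 290 (20% fewer) | 90.1% |
| 253 (30% fewer) | 87.8% |

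The number of CCS drives power, so losing children within CCS costs little.

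**5. Bias**

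If leaving depends only on arm and the T1 score, both are already in the post-on-pre model, and the effect estimated among children with both scores is unbiased when the T1 relation is correctly modelled. In a simulation of 19 CCS of 19 children with no true effect, about 16% of T2 scores were missing, with dependence on T1 in opposite directions by arm. Over 4,000 runs the mean adjusted effect was −0.001 (Monte Carlo SE 0.002), against −0.17 without adjustment.

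**The case against.** The strongest reply is that an analysis set says who is included, and a missing-data method says how. With multiple imputation, or a likelihood that also models the covariate, the two statements are compatible, and a condensed article may leave that to a fuller plan. It is right that the model need not exclude anyone. But the article does not merely stay silent: it fixes both the set and the model for the behaviour outcomes, and as written the second cannot serve the first.

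Three further objections stand and limit the point.

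- **Scope.** A reader might infer that the whole trial fails to deliver its intention-to-treat set. The documents do not support that: the cortisol model and the classroom tally are different analyses, and only the child-level BEH ratings carry the conflict in this form.
- **Amount of loss.** Under Evaluation' adherence, a child absent on the visit day loses the saliva samples, but the questionnaires were completed on a day when the child was present. Loss of BEH scores would therefore come mainly from turnover and non-return, for which no rate is given. Independent missingness at T1 and T2 is also a crude description of leavers and joiners.
- **Bias.** A reader might infer that dropping these children biases the behaviour effect. Where leaving depends on arm and T1 score, it does not. Where it depends on the unobserved T2 behaviour, a joint model under missing-at-random is not protected either.

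Including T2-only children also has a price: some may have joined a CCS after its allocation was known.

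**Conclusion.** The point holds for the educator and parent BEH ratings. The article promises to analyse every consented child with either score and specifies a model that, as written, uses only children with both. It states no imputation or joint model for these outcomes that would close the gap.

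Under the assumed 5% to 20% independent missingness per score, 34 to 116 of 362 children would be promised but not analysed. These counts illustrate the gap and do not estimate it. The power cost is modest under the assumed d = 0.5 and ICC 0.05. What correction buys is an analysis that matches its intention-to-treat description, and somewhat better precision. It does not remove bias from loss that depends on unseen T2 behaviour. The contradiction should be resolved before analysis, but it does not undermine the design.

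**What to change.** For the BEH outcomes, enter the T1 and T2 scores jointly as responses, with one common T1 mean for both arms, random effects for CCS, educator group and child, and the arm difference at T2 as the estimand. Every child with at least one score then contributes. Multiple imputation that respects the clustering is an acceptable alternative. Add a sensitivity analysis limited to children enrolled at T1, because T2-only children may have joined after allocation was known.

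If the covariate model is kept without imputation, restate the behaviour analysis set as children with both scores, and do not describe it as all children with at least one assessment.

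The cost is analysis-plan wording, slightly more analysis work and an explicit missing-at-random assumption. No new data are needed, and the article still describes these analyses in the future tense.

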### Data analysis

#### Testing the equivalence of the intervention and control groups at baseline

We will compare the intervention and control groups on a wide range of family, health and child variables assessed at pre-intervention to test whether the randomization procedure was successful in yielding equivalent groups. This is a first step in examining the extent to which biological and behavioral impacts observed in post-intervention are associated with the Minipally intervention, and not to confounding differences at baseline between treatment groups. Specifically, group differences will be examined for socio-demographic information (age, income and education of the parents, household composition); child variables such as the rates of disruptive behaviors; and CCS related variables such as number of hours attending child care services per week, number of months attending a child care service. If differences are detected, these variables will be statistically controlled for in subsequent analyses.

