#### General health questionnaire assessed by parents

Parents filled out a short questionnaire in pre and post-intervention upon CCS arrival to obtain information about a wide range of factors known to potentially affect cortisol secretion, including the child’s general health (infection, allergies, temperature, a tooth or ear ache, fracture or a sprain); sleep quality during the previous night (bedtime, wake-time, night-waking length, quality of sleep); his/her mood at the arrival to the CCS (fatigued, happy, sad, worried, excited, angry); chronic or serious health concern (juvenile diabetes, asthma, cardiac problems, had undergone surgery or been hospitalized in the last year); use of prescription or non-prescription drugs in the last 24 h; and the food consumed in the morning of the assessment (time of breakfast, quantity of dairy product consumption, time of snacks taken after breakfast) [31].

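### Covariates are selected by detected baseline imbalance and by screening cortisol factors on trial data, without limiting the cortisol factors to pre-intervention values

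*Protocol article*

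**What the plan says.** Two covariate rules are stated in the Protocol article.

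**Baseline rule.** Under Testing the equivalence of the intervention and control groups at baseline, the arms are compared "to test whether the randomization procedure was successful in yielding equivalent groups". The consequence is: "If differences are detected, these variables will be statistically controlled for in subsequent analyses". The list is open-ended. Seven variables are named: age, income, education, household composition, disruptive behaviour, weekly hours in CCS and months in CCS. No threshold is given.

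**Cortisol rule.** Under Stress regulation, after outlier handling and log transformation: "We will then use univariate and multivariate models to assess several factors known to potentially affect cortisol secretion". Sleep, health and medication are given as examples, and these factors are then controlled for in later analyses. The General health questionnaire section describes the source of such factors: "Parents filled out a short questionnaire in pre and post-intervention upon CCS arrival". It covers the previous night's sleep, medication in the last 24 h, health and "his/her mood at the arrival to the CCS (fatigued, happy, sad, worried, excited, angry". Table 1 lists this questionnaire as a potential confounder at both time points.

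The one covariate fixed in advance is pre-intervention behaviour, in the behaviour models (Child behaviors). The model under Determination of sample size contains treatment, a baseline term and random effects, and no other covariate.

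**The concern.** Allocation was by a computer-generated sequence. A difference between arms on a baseline variable therefore says little about whether that variable predicts the outcome, and prediction is what makes adjustment worthwhile. A rule triggered by imbalance can add irrelevant variables that happened to differ and omit prognostic ones that did not. With 19 randomised units, each added covariate is costly and each omitted prognostic one is a loss.

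The cortisol rule raises a different problem. The outcome is the post-intervention diurnal slope. Many questionnaire items describe the day of sampling or the night before it, so post-intervention values are the ones that would explain post-intervention cortisol. They are collected after 8 months of a programme that teaches self-regulation and emotional expression, from parents who know the allocation. If the programme changes sleep or mood, adjusting for them removes part of its effect.

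**Working it through.** **1. The plan's own figure.** The document gives no figure for either covariate rule. Its only design figure is that "19 child care services would allow to detect a medium size effect of the intervention on the selected outcomes", with 90% power at two-sided 5%. No ICC or numeric effect is given. Assume d = 0.5, and take 10 v 9 CCS (Abstract), "2 groups per child care center" and 8 children per group (Child behaviors). With a common ICC of 0.0535:
- variance of a CCS mean = [1 + 7(0.0535) + 8(0.0535)]/16 = 1.803/16 = 0.1127
- SE = √(0.1127 × (1/10 + 1/9)) = 0.154
- 0.5/0.154 = 3.24, and 3.24 − 1.96 = 1.28, which is 90% power.

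So 90% is attainable at an ICC near 0.054 (normal) or 0.040 (t, 17 df). It cannot be confirmed, and it does not bear on the covariate rules.

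**2. How often the baseline rule is triggered by chance.** Assume independent variables and a 5% threshold.
- Seven named variables: 1 − 0.95^7 = 0.302.
- Six, if disruptive behaviour is set aside because the behaviour models already contain it: 1 − 0.95^6 = 0.265.
- If the open-ended list grows to 10 or 20 variables: 0.401 or 0.642.

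**3. What the rule does to inference.** Simulation on CCS means: 10 v 9, seven independent covariates, each with coefficient r (0 to 0.35) on the outcome, 6,000 runs per setting, effect 0 or 1 SD of the CCS means. No fixed T1 outcome covariate was included.

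| Quantity | Unadjusted | Detect-then-adjust | All seven fixed |
|---|---|---|---|
| Type I error | 0.044–0.056 | 0.036–0.051 | 0.045–0.053 |
| Power, r = 0 | 0.532 | 0.480 | 0.337 |
| Power, r = 0.15 | 0.540 | 0.503 | 0.386 |
| Power, r = 0.25 | 0.527 | 0.491 | 0.521 |
| Power, r = 0.35 | 0.536 | 0.512 | 0.960 |

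Mean bias of the rule was within 0.01 SD throughout. Its significance verdict differed from the unadjusted one in 1–3% of null trials and 7–10% of trials with an effect. It had lower power than no adjustment in every row. When covariates were strongly prognostic it gained almost none of what a fixed set gains. The last column also shows that a fixed set must be short: seven non-prognostic covariates cut power from 0.53 to 0.34.

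**4. Adjusting for a post-intervention covariate.** Assume a total effect of 0.50, a programme-to-covariate effect a and a covariate-to-cortisol effect b. Without a shared cause the adjusted estimate is 0.50 − ab.
- a = 0: 0.50, no bias.
- a = b = 0.2: 0.50 − 0.04 = 0.46, a loss of 8%.
- a = b = 0.4: 0.50 − 0.16 = 0.34, a loss of 32%.

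If an unmeasured cause with coefficient 0.3 acts on both covariate and cortisol (unit residual variances), the covariate slope rises by 0.09/1.09 = 0.083. The estimate at a = b = 0.4 is then 0.50 − 0.4 × 0.483 = 0.307 (simulated 0.302), a loss of about 39–40%.

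**The case against.** **The tempting stronger readings.** A reader might infer four things that the document does not support.
- *That the baseline rule biases the estimate or invalidates the 5% level.* The simulation shows neither: mean bias is about zero and the level is nominal to conservative.
- *That false flags are far more frequent because children are tested as if independent.* Ignoring clustering with 16 children per CCS would give 47%, 65% and 82% for seven variables at ICC 0.02, 0.05 and 0.10. But the article does not say that the baseline tests ignore clustering, and it commits the behaviour models to the nested structure.
- *That an imbalance too small to be flagged leaves a large shift in the estimate.* Pre-intervention behaviour is always in the behaviour models and absorbs part of any such shift. Chance imbalance is also sampling variation that the standard error already reflects.
- *That post-intervention mood will be adjusted for.* Mood is not among the examples under Stress regulation. It enters only through the questionnaire section, and the article does not say which time point's values are used. This limb is therefore conditional.

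**Other points for the plan.** The article uses the language of testing and detection, but never writes of significance and gives no threshold; 5% is assumed here. Parents could refuse assessment and knew the allocation after randomisation. The article does not say whether consent came first, so comparing the arms at baseline could reveal selective participation. That supports showing the comparison, but not letting it choose the model. Finally, a journal article may leave the covariate list to the SAP. That is fair for the list, but both selection rules are stated here, and a SAP that follows them inherits the problem.

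**Conclusion.** The point holds in this form. The baseline rule makes the primary model depend on observed imbalance instead of prognostic value. With seven independent variables at an assumed 5% level, about 30% of trials would trigger it by chance. The harm is lost precision and a verdict that can turn on chance imbalance, not bias or an inflated error rate. The simulated figures are illustrative, because they use independent covariates and no T1 outcome term.

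The cortisol rule is open on the matter that counts most: it does not restrict adjustment to pre-intervention values. If post-intervention values are used and the programme affects them, the estimate is no longer the total effect. The 8–40% attenuation rests wholly on assumed path effects of 0.2–0.4, the upper end with a shared cause. If the programme does not affect these factors, there is no bias from this source.

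**What to change.** - Report baseline characteristics by arm descriptively, and delete the rule that a detected difference triggers adjustment.
- Before unblinding, prespecify a short covariate set for the primary models on prognostic grounds: the T1 value of the outcome (including T1 cortisol in the cortisol model) plus one or two baseline variables, such as parental income or education and weekly hours in CCS. Keep it short because there are only 19 CCS.
- For cortisol, add clock time of sampling on prior knowledge, not after screening on trial data.
- Use all T2 parent-reported factors (mood, sleep and wake time, health, medication) in a sensitivity analysis only. Wake time and medication in the last 24 h come from the same T2 questionnaire, so they are post-randomisation as well and belong there.

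The cost is analysis-plan wording. The variables are already collected. For clock time this assumes that actual sampling times were logged, since the article states only the collection windows.
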